### 2.7. Statistics

#### 2.7.1. Sample Size

The study is a randomized, double-blinded, active-sham controlled design, the statistical experts decided on a 1:1 sample ratio for the experimental group to the control group. Based on the previous literature reports, the treatment response rate of different DBS targets for refractory OCD should range from approximately 40% to 60% [38], and previous studies showed that the remission rate of patients with OCD who do not receive any treatment is around 10% [39]. Therefore, the estimation of the overall efficacy of the experimental group is set to the median of 50%; the estimation of the overall effectiveness of the control group is set at 10%. This study is designed as a differential test to determine whether the mean of the experimental group (u1) is different from that of the control group (u2). The hypotheses are as follows: H0: u1 − u2 = 0, H1: u1 − u2 ≠ 0. A two-sided significance level was set at 5% and statistical power at 90%, with a maximum acceptable drop rate of 20%. The total sample size of the study was 64, and the size of each group was 32. The sample size was calculated by the PASS V.11 sample size calculation software (NCSS, Kaysville, UT, USA). 

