DBS is a promising therapeutic approach for patients with treatment-refractory OCD. Based on the classical cortico-striato-thalamo-cortical (CSTC) circuit dysfunction model of OCD [15,16], the typical DBS targets implied in refractory OCD include the anterior limb of internal capsule (ALIC), ventral striatum (VS), the subthalamic nucleus (STN), and midbrain targets [17,18]. In 1999, Nuttin et al. [19] first reported that the DBS of ALIC (ALIC-DBS) was effective for refractory OCD. In this study, four patients received ALIC-DBS treatment; three of them showed a significant alleviation in symptoms. Among these, one patient’s symptoms were reduced by over 90% based on the parents’ self-report. The combined long-term results from four centers supported the idea that ALIC-DBS has long-term effects on OCD symptoms and is well-tolerated [20]. The VS target mainly refers to the nucleus accumbens (NAcc). NAcc-DBS has been associated with reduced OCD symptoms and decreased excessive frontostriatal connectivity between NAcc and the lateral and medial prefrontal cortex, partially supporting the hypothesis of extreme frontostriatal connectivity being involved in OCD pathophysiology [21]. Anteromedial subthalamic nucleus DBS (amSTN-DBS) is another therapeutic option for treating severe and refractory OCD, and has been found to be associated with significant improvements in social adjustment and struggles in work, social, and familial life [22]. The midbrain DBS location targeted ascending fibers of the ventral tegmental area (VTA), which travel through the superior limb of the medial forebrain bundle (slMFB), to connect with the superior frontal gyrus, the middle frontal gyrus, and the lateral orbitofrontal regions [23,24], which also suggests its treatment potential for OCD. In addition, the bed nucleus of the stria terminals (BNST) and the inferior thalamic peduncle (ITP) also have been used as potential targets in many clinical trials, with positive results [25,26]. A clinical review has reported a response rate of 58.2% and a mean symptom reduction of 47.7% across all DBS targets with treatment-refractory OCD [27]; however, most of the current clinical evidence comes from open-label cohorts or randomized controlled trials with very small sample sizes. Wu et al.’s review suggests that the DBS implanted in the ventral anterior internal capsule represents an emerging, but not established, therapy; additional, well-designed, and blinded clinical trials are still needed [28]. Based on the aforementioned CSTC circuits dysfunction model, the VS, NAcc, and nearby ALIC have become the most common targets; however, the DBS implantation of NAcc or ALIC alone is currently not enough because it does not address the impairments in complex emotional and cognitive processing, as well as OCD symptoms. Combined multiple targets of DBS could be a novel direction for treatment-refractory OCD. 

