
Huys et al. [29] investigated the DBS of the combined anterior limb of internal capsule and nucleus accumbens (ALIC/NAcc-DBS) for refractory OCD for the first time. They reported a 40% response rate and a 33% reduction in Y–BOCS, indicating that ALIC/NAcc-DBS is a promising treatment option. However, this study was based on an open-label and small sample cohort, and the two targets were stimulated under the same parameters, which cannot effectively activate the two targets simultaneously. Previous studies have shown that the NAcc and ALIC are gray-matter neurons and white-matter fiber bundles, respectively, which require different parameters to show clinical benefits. A review of earlier clinical trials showed that the parameters used in ALIC were higher than those used in NAcc, especially voltage and pulse width [25,30,31,32,33]. 

The present study aims to explore the efficacy and safety of ALIC/NAcc-DBS for treatment-refractory OCD, based on a multicentered, randomized, double-blinded, and sham-controlled design. The DBS system used in this clinical trial adopts a multi-source stimulation mode, which means that different stimulation parameters can be used in NAcc and ALIC to simultaneously meet the effective stimulation requirements of the two neural structures. Custom tetrapolar electrodes will be used to achieve broad coverage of ALIC and NAcc. 

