## 3. Outcomes

### 3.1. Primary Outcome

The primary outcome is a comparison of the treatment response rate (TRR) of the active and sham-controlled groups at the third month after initial stimulation. (TRR is defined as the number of treatment responses/the number of groups, a ≥35% reduction in Y–BOCS plus CGI ≤ 2, meeting the treatment response criteria.) The safety evaluation is determined by spontaneous reports, and laboratory testing is reflected in AEs. As mentioned in the Methods section, all AEs will be documented throughout the whole study.

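### The 10% control rate behind the 90% power is remission in untreated patients, not response under sham, so the power is not shown to apply to the primary comparison

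*Protocol article*

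**What the plan says.** Section 2.7.1 (Sample Size) builds the calculation from these inputs:

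- **Active rate.** The section says that "the treatment response rate of different DBS targets for refractory OCD should range from approximately 40% to 60" per cent, and then "the estimation of the overall efficacy of the experimental group is set to the median of 50" per cent.
- **Control rate.** It says that "previous studies showed that the remission rate of patients with OCD who do not receive any treatment is around 10" per cent, and carries 10% over as the control group's effectiveness.
- **Hypotheses.** These are framed as a test of "whether the mean of the experimental group (u1) is different from that of the control group (u2"), with H0 a zero difference between u1 and u2.
- **Operating characteristics.** Two-sided 5%, 90% power, up to 20% dropout, 32 per group, 64 in total.

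Section 3.1 defines the primary outcome as a "comparison of the treatment response rate (TRR) of the active and sham-controlled groups" at month 3. A responder needs a Y-BOCS fall of at least 35% and CGI of 2 or less.

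Sections 2.3 to 2.5 describe the control arm. Sham patients have electrodes implanted, go through the same programming and evaluation as active patients, remain on stable medication, and are blinded along with programmers and assessors.

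On prior evidence, the Introduction says of one open-label study of the same combined target: "They reported a 40% response rate".

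**The concern.** The control input differs from the trial's control arm in two ways.

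- **Outcome.** The input is remission; the endpoint is response on a composite criterion. The active input, by contrast, is a response rate, so the two sides of the calculation are not on the same scale.
- **Condition.** The input comes from people receiving no treatment. The sham arm has surgery, programming sessions, blinded expectation of benefit and continuing medication.

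No sham or off-stimulation response rate appears anywhere in the article, so nothing in it links the 10% to the arm it represents. With about 26 completers per arm, a few percentage points in the control rate move the power a good deal. The Discussion describes this as the largest single-study sample to the authors' knowledge, so a null result would carry weight. A reader would take it as coming from a trial with 90% power against sham, and section 2.7.1 does not establish that.

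**Working it through.** **Inputs.** All from section 2.7.1: p1 = 0.50, p2 = 0.10, two-sided alpha 0.05 (z = 1.960), power 0.90 (z = 1.282), dropout 20%, 1:1 allocation.

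**Step 1: reproduce the stated N.** Two-proportion formula, pooled variance under H0, no continuity correction, with pbar = (0.50 + 0.10)/2 = 0.30:

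n = [1.960 × √(2 × 0.30 × 0.70) + 1.282 × √(0.50 × 0.50 + 0.10 × 0.90)]² / (0.50 − 0.10)²

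= (1.270 + 0.747)² / 0.16 = 25.4 per arm.

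Allowing for dropout: 25.4 / 0.80 = 31.8, so 32 per arm and 64 in total. This matches the article. (Rounding to 26 before the dropout step gives 33 per arm and 66 in total, a difference of two patients.)

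The figure thus comes from a comparison of proportions. The wording about means plays no part in it.

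**Step 2: power when the rates differ from 50% and 10%.** With 20% dropout, 32 × 0.80 = 25.6, taken as 26 completers per arm. For each pair of true rates, all possible outcomes (a responders of 26, b responders of 26) were enumerated. Their binomial probabilities were summed wherever the uncorrected chi-square test rejects at two-sided 5%.

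The active rates are the ends and midpoint of the 40–60% range in section 2.7.1; 40% is also the figure from the Introduction. The 10% column is the article's value. The 5%, 15% and 20% columns are assumptions, because the article gives no sham rate.

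| Active | Sham 5% (assumed) | Sham 10% (article) | Sham 15% (assumed) | Sham 20% (assumed) |
|---|---|---|---|---|
| 40% | 92% | 75% | 55% | 37% |
| 50% | 98% | 92% | 81% | 65% |
| 60% | >99% | 99% | 95% | 87% |

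If all 32 per arm complete, the loss shrinks but remains: 40 vs 10 gives 83%, 50 vs 15 gives 88%, 50 vs 20 gives 73%, 40 vs 20 gives 42%.

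**Step 3: read the table.** The 40 vs 10 cell uses only the article's own figures and is already at 75%. At the planned 50% active rate, moving the assumed sham rate from 10% to 20% takes power from 92% to 65%. Moving it to 5% raises power to 98%.

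**The case against.** **The sham rate may be at or below 10%.** Section 2.2.1 requires failure of at least three drug trials, augmentation with at least two antipsychotics and at least 20 sessions of exposure therapy. Medication is held stable, and response needs both parts of a composite. The 10% source is described only as patients with OCD, not refractory ones. This stands. A reader might infer that the true power is below 90%, or lies somewhere like 37–75%. The article does not support that: across active 40–60% and an assumed sham rate of 10–20%, power runs from 37% to 99%, and the 37% needs the least favourable value on both sides.

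**The 50% is a defensible judgement.** It is the midpoint of the cited range. The Introduction also explains that the earlier 40% study stimulated both targets with the same parameters, whereas this trial uses separate ones. This stands too; 40% belongs in a range and is no proof that 50% is wrong.

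**The active range need not be open-label.** A reader might infer that it is, since the Introduction says "most of the current clinical evidence comes from open-label cohorts or randomized controlled trials with very small sample sizes". That sentence describes the DBS literature in general. Nothing states what kind of studies lie behind the 40–60%, so this cannot be held against the calculation.

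**The reference to means might seem to undermine the power.** It does not, because N reproduces from proportions.

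**A condensed article may leave sensitivity tables to the full protocol or the SAP.** That is fair, and the lack of a table is not the fault here. The fault is that the article states a basis for the control rate, and that basis is for a different outcome and condition. None of the objections removes that mismatch.

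**Conclusion.** The point holds in a limited form. The control rate in section 2.7.1 is drawn from untreated remission, while the trial compares response against blinded sham after implantation. The 90% is correct arithmetic for 50% against 10%, but it is not shown to be the power of the primary comparison. Whether the true sham rate is above or below 10% cannot be decided from the article, so neither can the direction of the error. What can be shown is the sensitivity: 75% at 40 vs 10 on the article's own numbers, and 65% to 98% at 50% active as an assumed sham rate runs from 20% down to 5%. These figures assume 26 completers per arm and an uncorrected chi-square test. The wording about means is a separate error of expression with no effect on N.

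**What to change.** Keep N = 64 and revise section 2.7.1:

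1. Write the hypotheses for the response rate: H0: p_active − p_sham = 0 against H1: p_active − p_sham ≠ 0.
2. Remove untreated remission as the basis for 10%. Either support the control rate with sham or off-stimulation response under the section 3.1 definition, or label 10% plainly as an assumption.
3. State that 90% power holds for 50% vs 10%. Give power for active rates of 40–60% over an assumed sham range that extends both below and above 10%.

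The cost is one paragraph and a small table. No patients are added, and the endpoint and analysis are untouched. The sponsor gives up an unconditional claim of 90% power.

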#### 2.7.2. Data Management

The electronic data collection (EDC) system will be used to collect all experimental data. The EDC system was rigorously tested and is fully compliant with the criteria of the Code of Quality Management for Clinical Trials of Medical Devices and the Technical Guide to Data Management in Clinical Trials. System testing and training of relevant personnel will be conducted before the EDC is officially enabled. When formally enabled, the researchers will be provided with an account number and password. The account is related to the user’s responsibilities and permissions. The relevant personnel shall properly hold the account information and shall not disclose the account information to others.

#### 2.7.3. Data Analysis

We will prepare the statistical analysis plan (SAP) based on the research program and database, applying the Statistical Analysis Software (SAS) version 9.4. Descriptive statistics use standard deviations or medians with interquartile ranges for continuous variables (depending on data distributions) and proportions for categorical variables. The comparison of group differences will be conducted using appropriate differentiate testing depending on the data type, including paired or group *t*-tests, analysis of variance (ANOVA), Wilcoxon rank-sum test, Kruskal–Wallis H rank-sum test, Chi-square test, Cochran Mantel Haenszel (CMH), etc. The significant level α will be set as 0.05 with the two-tailed test, and statistical uncertainty will be expressed in 95% confidence intervals (CI). 

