### 3.2. Secondary Outcomes

The secondary outcomes are comparisons of change in Y–BOCS, CGI, HAMD, and HAMA scores at the third and sixth months compared to baseline between the active and sham-control groups, as well as the scores of the third month minus the sixth month between the two groups. 

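### The only continuous-data tests the article names for the secondary change scores do not condition on the recorded baseline; baseline-adjusted ANCOVA would be at least as precise in large samples

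*Protocol article*

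**What the plan says.** Protocol article, section 3.2 (Secondary Outcomes), sets between-arm "comparisons of change in Y–BOCS, CGI, HAMD, and HAMA scores at the third and sixth months compared to baseline". It adds a between-arm comparison of the difference between months 3 and 6.

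Section 2.7.3 (Data Analysis) says that a SAP will be prepared and that tests will be chosen by data type. The named examples begin with paired or group t-tests and go on to "analysis of variance (ANOVA), Wilcoxon rank-sum test, Kruskal–Wallis H rank-sum test, Chi-square test, Cochran Mantel Haenszel (CMH), etc". No test is tied to an endpoint. ANCOVA, regression and mixed models are not named, and no covariate is mentioned.

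Section 2.3 (Procedures) has Y–BOCS, HAMA, HAMD and CGI taken at the preoperative baseline visit, so the values needed for adjustment will be in the database.

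**The concern.** A t-test, one-way ANOVA or rank test on change scores does use the baseline, but only by subtracting it. That forces the slope of follow-up on baseline to be exactly 1. If the true slope differs from 1, part of any chance baseline difference between arms stays in the estimate and the variance is larger than it need be. ANCOVA estimates the slope from the data.

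Arms of 32 leave room for chance imbalance, and recruiting more implanted patients is not an easy way to gain precision. What is at stake is the width of the confidence intervals for the continuous secondary outcomes, Y–BOCS change above all.

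**Working it through.** **The plan's own figure.** Section 2.7.1 assumes response rates of 50% and 10%, two-sided 5%, 90% power, 1:1 allocation and 20% dropout. With pooled variance and no continuity correction:

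- n per arm = [1.960·√(2·0.3·0.7) + 1.282·√(0.25 + 0.09)]² / 0.4² = 25.4.
- 25.4 / 0.8 = 31.8, so 32 per arm and 64 in total.

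The stated 64 is reproduced. (Rounding to 26 before allowing for dropout gives 33 per arm.) It rests on the binary response rate, so nothing below changes it.

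**Chance baseline imbalance.** The SD of the baseline difference between arms, in baseline SD units, is √(2/n): √(2/32) = 0.25 with full arms, and √(2/26) = 0.28 with about 26 per arm after 20% dropout.

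**Variance comparison.** Let r be the baseline-to-follow-up correlation and k = baseline SD / follow-up SD. In units of follow-up variance:

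- change score: 1 + k² − 2rk
- ANCOVA residual: 1 − r²
- ratio of ANCOVA to change score: (1 − r²) / (1 + k² − 2rk)

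The denominator equals (1 − r²) + (k − r)², so the ratio never exceeds 1. It equals 1 exactly when r = k, that is, when the true slope r/k is 1.

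The documents give neither r nor k. Both are assumed.

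| k | r | Ratio | Saving |
|---|---|---|---|
| 1 | 0.2 | 0.60 | 40% |
| 1 | 0.5 | 0.75 | 25% |
| 1 | 0.8 | 0.90 | 10% |
| 0.7 | 0.3 | 0.91/1.07 = 0.85 | 15% |
| 0.7 | 0.5 | 0.75/0.79 = 0.95 | 5% |
| 0.7 | 0.7 | 0.51/0.51 = 1.00 | 0% |
| 0.5 | 0.2 | 0.96/1.05 = 0.91 | 9% |
| 0.5 | 0.4 | 0.84/0.85 = 0.99 | 1% |
| 0.5 | 0.5 | 0.75/0.75 = 1.00 | 0% |
| 0.5 | 0.7 | 0.51/0.55 = 0.93 | 7% |
| 0.5 | 0.8 | 0.36/0.45 = 0.80 | 20% |

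At k = 1 and r = 0.5, 64 patients analysed by ANCOVA match 64/0.75 ≈ 85 analysed by change score, and a comparison with 80% power rises to about 90%.

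**Why k matters here.** Section 2.2.1 requires a Y–BOCS of at least 25 at entry. That narrows the baseline spread, while follow-up scores may spread out as some patients respond and others do not. So k below 1 is plausible for Y–BOCS. The entry floor does not apply to HAMD or HAMA.

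**Small-sample cost.** Estimating one slope multiplies the ANCOVA variance by about 1 + 1/(2n − 4): 1 + 1/60 = 1.017 at n = 32 and 1 + 1/48 = 1.021 at n = 26. The price is therefore about 2%, which matters only if r is very close to k.

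**The case against.** The strongest reply is that section 2.7.3 gives an open, illustrative list and defers to a SAP, where covariates for secondary outcomes are normally set. This stands in part. The article does not commit the trial to unadjusted tests, and the absence of a full model is no error. But the article did choose to name methods, and every one it names for continuous data leaves out the baseline covariate.

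Several stronger readings are tempting, and the documents do not support them:

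- **That the analysis ignores centre.** CMH is a stratified test and ANOVA can carry a centre factor. The article does not say whether either will be used that way.
- **That change scores lose precision whenever r is below 1, with gains of 18% to 54% in effective sample size.** Those gains come from (1 + r)/2 at r = 0.7 and 0.3 and need equal SDs. With k = 0.5 and r = 0.5 there is no gain. The entry floor might be read as making the loss larger, but it can also lower k and shrink the loss.
- **That chance imbalance biases the result.** Under randomisation the change-score difference is unbiased. Imbalance is part of its sampling variance and is already reflected in the confidence interval.
- **That the primary comparison is weakened.** It is binary, and section 2.7.1 plans it with "statistical power at 90" per cent. That calculation is reproduced above.

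A further fair point is that centre terms would use 5 to 6 degrees of freedom with roughly 52 completers (2 × 26). That argues against making them compulsory, not against adjusting for baseline.

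**Conclusion.** The point holds for the continuous secondary outcomes only, as an improvement worth making and not as an error that invalidates the plan. The named tests are valid, but in large samples they are never more precise than a baseline-adjusted analysis.

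The size of the gain cannot be derived from the documents. Under assumed values, the variance saving is about 10–40% with equal SDs (r from 0.8 down to 0.2). With a baseline SD half that at follow-up, it is about 0–9% for r from 0.2 to 0.7, and 20% at r = 0.8. The possible loss is about 2% when r is close to k. For Y–BOCS, with its entry floor, the lower end of the gain is quite possible.

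**What to change.** In the SAP, fixed before unblinding:

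- For Y–BOCS, HAMD and HAMA at month 3, and likewise at month 6, make the main analysis an ANCOVA, or an equivalent mixed model, of the follow-up score on arm and the same scale's baseline score. Report the adjusted difference with its 95% CI.
- Keep the rank tests as sensitivity analyses.
- For CGI, state which rating is used. Section 2.3 lists it at baseline among measures of symptom severity, while section 3.2.2 describes it as improvement or worsening relative to baseline. A same-scale baseline covariate applies only if a severity rating is taken at baseline.
- Treat a centre factor or stratum as optional. First reconcile the centre count, since section 2.1 states six centres but names seven institutions.

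The cost is one degree of freedom per model, a few lines of SAS code and a sentence or two of text. No new data are needed, and the primary analysis and sample size stay as they are.

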## 3. Outcomes

### 3.1. Primary Outcome

The primary outcome is a comparison of the treatment response rate (TRR) of the active and sham-controlled groups at the third month after initial stimulation. (TRR is defined as the number of treatment responses/the number of groups, a ≥35% reduction in Y–BOCS plus CGI ≤ 2, meeting the treatment response criteria.) The safety evaluation is determined by spontaneous reports, and laboratory testing is reflected in AEs. As mentioned in the Methods section, all AEs will be documented throughout the whole study.

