## Abstract

Backgrounds: Deep brain stimulation (DBS) is an emerging and promising therapeutic approach for treatment-refractory obsessive-compulsive disorder (OCD). The most common DBS targets include the anterior limb of internal capsule (ALIC) and nucleus accumbens (NAcc). This protocol aims to explore the efficacy and safety of the combined ALIC- and NAcc-DBS for treatment-refractory OCD. Methods: We will recruit 64 patients with refractory OCD from six centers, randomly allocate them to active and sham-stimulation groups through a three-month double-blind phase, then enter a three-month open-label phase. In the open-label stage, both groups experience real stimulation. Outcome measures: The primary outcome will be the efficacy and safety of combined ALIC- and NAcc-DBS, determined by treatment response rate between the active and sham-stimulation groups at the double-blind stage and spontaneously reported adverse events. The secondary outcomes are comparisons of change in Y–BOCS, CGI, HAMD, and HAMA scores at the third and sixth months compared to baseline between the active and sham-control groups, as well as the scores of the third month minus the sixth month between the two groups.

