### 2.3. Procedures 

According to the inclusion criteria, the participants must attest to maintaining stable pharmacological treatment for two months preceding DBS surgery and throughout participation in the DBS trial until the end of the follow-up. The visit time points include a screening visit, preoperative baseline visit, perioperative period, programming/stimulation adjustment, double-blind visit, open-label visit, and extended one-year observation. The flow chart is shown in Figure 1. 

During the screening visit, patients who meet the criteria for refractory OCD are screened after signing informed consent. At this stage, patients undergo a series of laboratory and imaging examinations to exclude potential contraindications for surgery or DBS treatment, including blood routine, urine routine, alanine aminotransferase (ALT), aspartate aminotransferase (AST), creatinine, urea nitrogen, blood coagulation, blood pregnancy (exclusively for women of childbearing age), electrocardiogram, chest X-rays, cerebral magnetic resonance imaging (MRI) or head CT, etc. 

The preoperative baseline visit will take place two weeks before the DBS operation. Patients will be screened according to existing inclusion/exclusion criteria, then undergo the clinical interview and a battery of clinical assessments. Demographic information (including age, gender, education, etc.), past and current medication status, and other clinical information will be recorded at baseline. The Y–BOCS and Y–BOCS symptom checklist will be used to assess the severity of OCD symptoms and list all the OCD symptoms. The Mini-International Neuropsychiatric Interview (MINI) will be used to screen comorbid DSM-5 psychiatric disorders. The Columbia suicide severity rating scale (C−SSRS) will be used to assess suicidal ideas or behaviors in participants. The Hamilton anxiety scale (HAMA), Hamilton depression scale (HAMD), and clinical global impressions (CGI) scale will be used to measure the severity of clinical symptoms. The Chinese versions of all measures have been shown to be reliable and valid. 

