After surgery, a 1.5 T MRI will be conducted in all participants to ensure that the electrodes are in the targeted position and the lead placement is accurate. Then, all patients will be randomized and assigned to the active-stimulation group (experimental group), and the sham-stimulation group (control group) by a randomized allocation system (SceneRay, Suzhou, China), and then integrated into the programmer according to the randomization plan. About 2–4 weeks after surgery, patients will undergo the first programming to adjust the stimulus parameters when recovering from cerebral edema. The parameters are optimized and individualized based on the acute effects on mood, anxiety, or self-reported OCD symptoms. During the exploration, subjects should not actively be exposed to an obsessive-compulsive symptom-inducing situation to assess their response to stimulation parameters. The active and sham-stimulation groups will be evaluated in the same way. During the study, the parameters will remain unchanged, unless for medical reasons. 

After the initial parameter optimization phase, patients enter a three-month, double-blind follow-up process, during which the active group is stimulated (ON phase) while the sham group is not (OFF phase). After that, the allocation is uncovered, patients enter a three-month, open-label, follow-up process, the sham group switch to a true stimulation of DBS, and the experimental group maintains the original stimulation. At the end of the double-blind and open-label processes, patients are evaluated using standardized psychiatric questionnaires (Y–BOCS, CGI, HAMD, HAMD, and C-SSRS). In addition, each patient’s medication will be recorded and maintained at a stable dose, so that we can investigate the effect of stimulation as a single therapy. Patient recruitment and screening are currently underway.

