## 4. Discussion

To the best of our knowledge, this is the first multicentered, double-blinded, sham-controlled study protocol to evaluate the therapeutic efficacy and safety of bilateral ALIC/NAcc-DBS for patients with treatment-refractory OCD. The sample size of this study protocol was relatively large; to the best of our knowledge, it is the largest sample size in a single study worldwide at present. The size of the Chinese population ensured that we could recruit enough eligible patients. 

The main concerns are the risks of any DBS neurosurgical procedure and long-term neuro-modulation. The neurosurgical-related side effects mainly include postoperative pain or discomfort, intracranial hemorrhage, infection, etc. These are mainly avoided by surgical operation. In this study, the surgeons will have extensive experience in neurosurgery and experience in DBS implant surgery. On the other hand, the risks related to long-term neuro-modulation mainly include new illness or injury, worsening or acceleration in previous condition, insomnia, hypomania, mania, and most seriously, seizures. According to previous studies, seizures emerged after 2–5 years of stimulation. To better observe the long-term adverse effects of neuro-modulation, we designed a one-year extended observation after the open-label trials.

In conclusion, this study is a multicentered, double-blinded, sham-stimulation-controlled study to investigate the efficacy and safety of ALIC/NAcc-DBS for refractory OCD. We hope that our study will benefit the patients who participate. We also hope that this study could extend DBS target options in future studies, to help patients who suffer from treatment-refractory OCD. 

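### Safety in the primary outcome rests on spontaneous reports, so named psychiatric stimulation effects may be incompletely captured in the only randomised phase, and the scheduled C-SSRS has no outcome role in the article

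*Protocol article*

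**What the plan says.** The abstract defines the primary outcome as efficacy and safety together, "determined by treatment response rate between the active and sham-stimulation groups at the double-blind stage and spontaneously reported adverse events". Section 3.1 (Primary Outcome) repeats the rule for safety: "The safety evaluation is determined by spontaneous reports, and laboratory testing is reflected in AEs". It then refers back to the Methods for the recording of all adverse events.

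Section 2.6 (Adverse Events) commits to recording every adverse event during the study and including it in the final analysis, and lists the fields to record. It does not say how events are elicited. Its list of possible events is mainly surgical and neurological. It names no mood event but is left open-ended.

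Section 2.3 (Procedures) introduces the C-SSRS at baseline, where it "will be used to assess suicidal ideas or behaviors in participants". It rates the scale again at the end of the double-blind and open-label phases, in a battery that includes "HAMD, HAMD, and C-SSRS" (the doubled HAMD is presumably a slip for HAMA). Section 3.2 (Secondary Outcomes) lists "comparisons of change in Y–BOCS, CGI, HAMD, and HAMA scores at the third and sixth months compared to baseline", without the C-SSRS.

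The Discussion names, among the risks of long-term neuromodulation, "insomnia, hypomania, mania, and most seriously, seizures".

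**The concern.** How adverse events are found is a rule of data collection, and this article states one. Under spontaneous reporting, an event enters the data when someone brings it up. Insomnia, hypomania and mania are events that a patient may not mention or may not regard as harm, so a rule without direct questions risks missing some of them.

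The timing makes this matter. All patients are implanted, and section 2.3 places randomisation after surgery, so operative events say little about active against sham stimulation. Stimulation effects are where the arms should differ. After month 3 the allocation is uncovered and the sham group is switched on, so no randomised contrast on harm remains. An analysis plan written later can add tables, but it cannot recover events that nobody asked about.

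The C-SSRS is a separate gap. It is a structured suicidality rating, taken in both arms at the end of the blinded phase, in a trial that excludes severe suicide risk at entry (section 2.2.2). The article gives it no outcome role, while Y–BOCS, CGI, HAMD and HAMA all have one.

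**Working it through.** **1. The plan's own figure.** The only sized quantity is the response rate (section 2.7.1): 50% against 10%, two-sided 5%, power 90%, dropout 20%, 64 patients in total. With pooled variance and no continuity correction:

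n = [1.960 × √(2 × 0.30 × 0.70) + 1.282 × √(0.50 × 0.50 + 0.10 × 0.90)]² / 0.40² = 25.4, so 26 per arm.

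Allowing for dropout, 26 × 1.2 = 31.2, so 32 per arm (64 in total), and 26 / 0.8 = 32.5, so 33 per arm (66). The stated 64 is reproduced. It does not bear on safety, for which the article gives no rate, hypothesis or sample size.

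**2. The passages side by side.**

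| Item | Where it is collected | Where it is an outcome |
|---|---|---|
| Adverse events | 2.6, all recorded; elicitation not described | 3.1 and abstract, by spontaneous reports |
| Insomnia, hypomania, mania | No direct questioning described | Only if they surface as adverse events |
| Depression, anxiety | HAMD, HAMA | 3.2 |
| Suicidality | C-SSRS at baseline and both phase ends (2.3) | None named |

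On the article's own descriptions, HAMD and HAMA rate depression and anxiety, and the C-SSRS rates suicidality. None is presented as a measure of hypomania or mania.

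**3. What incomplete capture does.** Let p_A and p_S be the true event probabilities in the active and sham arms, and c the fraction captured, equal in both arms. Then:

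- observed risk difference = c·p_A − c·p_S = c·(p_A − p_S), which shrinks in proportion to c;
- observed risk ratio = (c·p_A)/(c·p_S) = p_A/p_S, which does not change.

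The documents supply none of p_A, p_S or c. The table uses assumed values only, with 32 per arm. Each cell gives expected counts (active against sham) and the risk difference in percentage points.

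| Assumed true rates | Ratio | c = 100% | c = 75% | c = 50% | c = 25% |
|---|---|---|---|---|---|
| 20% vs 5% | 4 | 6.4 vs 1.6; 15 | 4.8 vs 1.2; 11.25 | 3.2 vs 0.8; 7.5 | 1.6 vs 0.4; 3.75 |
| 30% vs 10% | 3 | 9.6 vs 3.2; 20 | 7.2 vs 2.4; 15 | 4.8 vs 1.6; 10 | 2.4 vs 0.8; 5 |
| 40% vs 10% | 4 | 12.8 vs 3.2; 30 | 9.6 vs 2.4; 22.5 | 6.4 vs 1.6; 15 | 3.2 vs 0.8; 7.5 |

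The ratio is the same across each row, but it rests on fewer events as c falls and so is estimated less precisely.

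**The case against.** The strongest reply is that section 2.6 already requires every adverse event to be recorded and analysed, and nothing says that an event seen by an investigator would be discarded. This stands as far as it goes: the plan does not limit the data to what patients volunteer, and laboratory findings also enter as adverse events. But recording what surfaces is not the same as asking, and the article's only statement on ascertainment is spontaneous reporting.

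A second reply is that HAMD and HAMA are compared by arm, so part of any psychiatric worsening is measured systematically. That is true of depression and anxiety, not of hypomania or mania.

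A third is that the Discussion ties these risks to long-term stimulation, places seizures at 2–5 years, and adds a one-year extension. The extension has no sham arm, however, and the article gives no onset time for insomnia, hypomania or mania. The blinded phase remains the only controlled look.

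Several stronger readings are tempting but not supported:

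- **That psychiatric events are under-counted.** This is a risk. No figure in the documents shows or sizes it.
- **That the C-SSRS data will go unused.** This would be inferred from silence in a condensed article. Section 2.7.3 says that an analysis plan will be prepared, and it could tabulate the scale.
- **That laboratory testing adds little after implantation.** The tests are listed at screening, but the flow chart is not shown, so the later schedule is unknown.
- **That the trial loses power for safety.** The plan states no safety test. For 30% against 10% at 32 per arm, power is about 52% even with full capture (53% by exact enumeration of the uncorrected chi-square test). Ascertainment alone is therefore not what would leave the comparison inconclusive.
- **That the device will look safer.** With equal capture this holds on the absolute scale only.

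**Conclusion.** The concern holds in a limited form. The safety part of the primary outcome is tied to spontaneous reports in two places. The psychiatric stimulation effects named in the Discussion are therefore at risk of incomplete capture in the only randomised comparison of stimulation harm. The C-SSRS is scheduled but assigned to no outcome in this article.

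The size of any under-count cannot be computed. Under equal capture in the two arms, which blinding makes plausible but does not guarantee, the absolute difference falls in proportion to the fraction captured and the ratio is unchanged. The figures in the table rest wholly on assumed rates and illustrate direction and scale only.

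The efficacy comparison is unaffected. The change is worth making now because the article reports recruitment and screening as under way, and events not asked about at month 3 cannot be recovered later.

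**What to change.** In section 3.1, and in matching words in the abstract, supplement spontaneous reports with a short fixed set of questions on the stimulation-related events named in the Discussion: insomnia, hypomania, mania and seizures. Ask them identically in both arms, by staff who do not know the allocation, at the existing month-3 visit before the allocation is uncovered, and repeat them at month 6. Report solicited and spontaneous events separately, so that the tables remain comparable with studies that used spontaneous reports alone. The operative events listed in section 2.6 need not be in the question set, because randomisation follows surgery and they would add little to the active against sham comparison.

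Name C-SSRS ideation and behaviour by arm at month 3, shown with baseline, as a descriptive safety outcome. Keep it separate from the new questions: it does not measure mania or insomnia and cannot replace them. No hypothesis test or change in sample size is needed.

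The cost is a few more minutes at two existing visits and one added table of data already scheduled. The downside is that more mild events will be recorded in both arms.
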